### Demographic information

Demographic data will be collected at baseline only from all the participating health visitors and families. The questionnaires will cover the following demographic information:Health visitors - age, gender, number of years working as a health visitor, local area of employment, number of years working in local area, any relevant post-qualification trainingFamilies - age of parent and child, gender of parent and child, parent’s relationship to child, parent’s age at birth of first child, parent’s current relationship status, partner’s relation to child, housing situation, employment status, income, parent’s level of education, and whether they have attended a parenting course previously

### Mediators

Factors that have previously been shown to mediate change in similar programmes [42, 43] will be investigated. These include change in parental behaviour, as measured by the Arnold-O’Leary Parenting Scale and the parenting behaviour categories of the DPICS observation tool, and change in maternal depression, as measured by the BDI.

### Moderators

The possible moderating role of high-risk factors (using the demographic questionnaire) such as poverty, unemployment, poor housing, single parenthood, young parenthood and lack of parental education as well as the presence of maternal depression (using the BDI), and other indicators of poor outcome will be investigated.

### Data collection

Parent measures will be collected during home visits by the research team, including observation of the parent–child interaction during a free play situation. Each parent will receive a gift (a children’s book) on completion of measures at each time point. The health visitor measure (health visitor demographic questionnaire) will be collected at the first day of EPaS 2014 training.

Research staff will be trained in coding the DPICS observational tool until 80% inter-rater reliability is achieved on all categories. At least 20% of observations at each time point will be coded simultaneously by two coders to establish inter-rater reliability. Frequent practice and trouble-shooting meetings will be held to maintain high reliability levels.

### Sample size

Previous research has shown the EPaS programme to be effective for families of children with behaviour problems [33, 34]; however, these studies were limited by small sample sizes and lack of a randomised control comparison. For the current study, to detect an effect size of 0.55 standard deviation on the ECBI at 80% power and 5% significance level, a total of 55 families in each condition would be required. With a 10% drop-out rate the estimated sample size increases to 60 families in each condition. Whilst acknowledging that an effect size of 0.55 standard deviation is optimistic, due to limited funds and time a larger sample would be difficult to recruit.

### Randomisation

On completion of baseline data collection, parents will be randomised to either an intervention or a waiting-list control condition on a 1:1 ratio. The process will be done within health visitors so that each health visitor has one intervention family and one waiting-list control family. The randomisation process will be undertaken by the second author using an online randomisation programme with random permuted blocks [44].

### Blinding

Due to the nature of the study, it is not possible to have a completely blinded design. Parents will know to which condition they have been allocated. Health visitors will also be aware of which participant is in the intervention and which in the waiting-list control condition. However, the research team undertaking the data collection will be blind to participant group allocation throughout the study. Baseline measures will be collected prior to randomisation and parents and health visitors will be asked not to reveal the group allocations to the research team at follow-up. A contamination procedure will be put in place if participants reveal their allocation to the researchers.

### Statistical analyses

Baseline characteristics of the sample (health visitor, parent, and child) will be analysed and checked for differences (if any) between the two conditions, intervention and waiting-list control and any differences will be recorded.

The main analyses will be performed using the entire intention-to-treat population. The primary outcome measure, the change in the scores on the parent-reported ECBI from baseline to follow-up, will be calculated for each individual and compared between conditions using multiple linear regressions, controlling for any differences in sample characteristics at baseline and the baseline scores on the ECBI. Study site will also be controlled for in the analyses to assess any effects of clustering.

Secondary outcome measures that assess changes from baseline to follow-up in child behaviour, parental practices, and parental depression will also be analysed using multiple linear regressions, controlling for any differences in sample characteristics at baseline, baseline scores of the relevant outcome measure, and study site. In addition to the intention-to-treat analyses, per-protocol analyses will be conducted on data from participants who have remained in the study and have completed measures at all time points.

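### Covariates beyond the baseline score and study site are chosen by observed baseline imbalance, so the primary model is not fixed before the arms are compared

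*Protocol article*

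**What the plan says.** The Statistical analyses section of the protocol article sets out two steps. First, a comparison of the arms: "Baseline characteristics of the sample (health visitor, parent, and child) will be analysed and checked for differences (if any) between the two conditions". Second, the result of that comparison feeds the model. The change in ECBI is compared by multiple linear regression, "controlling for any differences in sample characteristics at baseline and the baseline scores on the ECBI". The secondary outcomes follow the same pattern, "controlling for any differences in sample characteristics at baseline, baseline scores of the relevant outcome measure, and study site".

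Two adjustments do not depend on balance: the baseline score of the outcome being analysed, and site ("Study site will also be controlled for in the analyses to assess any effects of clustering"). Everything else is conditional on an observed difference. The section names no further covariate and does not say what counts as a difference.

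The variables open to the rule are at least those under Demographic information, where the family list begins "age of parent and child, gender of parent and child, parent’s relationship to child, parent’s age at birth of first child, parent’s current relationship status". The Moderator analysis section brings risk factors into regression models to study effect modification. It does not make them fixed covariates of the main analysis.

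**The concern.** Baseline measures are taken before randomisation, so if allocation is carried out properly any difference between the arms is chance. The size of a chance difference carries no information about whether the variable predicts the outcome. A rule driven by imbalance therefore tends to admit irrelevant variables and to leave out good predictors that happen to be balanced.

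Two things are at stake. The primary model cannot be written down until the arms have been compared, and with no criterion for a difference the analyst has discretion over its content. Precision available from data already collected is also given up. That matters here because the Sample size section itself calls the target effect optimistic and says a larger sample would be difficult to recruit.

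A smaller point concerns health visitor characteristics, which are among those to be compared between arms. The Randomisation section says: "The process will be done within health visitors so that each health visitor has one intervention family and one waiting-list control family". In intact pairs the two arms therefore contain the same health visitors, and the comparison can show nothing.

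**Working it through.** **The plan's own figure.** The Sample size section aims "to detect an effect size of 0.55 standard deviation on the ECBI at 80% power and 5% significance level" and gives 55 families per condition, raised to 60 for 10% drop-out. Sidedness is not stated; two-sided is assumed.
- Normal approximation: n = 2(1.96 + 0.842)² / 0.55² = 51.9, so 52 per arm. The t-test gives 52.9, so 53.
- Power at 55 per arm is 82.2% (normal) or 81.6% (t). With 60 × 0.9 = 54 evaluable, it is 81.5% or 80.8%.

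The stated 55 is slightly generous, and nothing below changes it.

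**How often chance alters the model.** The Demographic information section lists 13 family items: parent age, child age, parent gender, child gender, relationship to child, age at first birth, relationship status, partner's relation to child, housing, employment, income, education, and previous parenting course. Assume independent items and p<0.05 as the trigger.
- Expected number selected: 13 × 0.05 = 0.65.
- Chance of at least one: 1 − 0.95¹³ = 48.7%.
- Range: 33.7% with 8 candidates and 64.2% with 20. With 13 candidates and p<0.10 as the trigger it is 1 − 0.90¹³ = 74.6%.

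**What the selection does to error and power.** Simulation with 5,000 trials per scenario: 55 per arm, 13 independent candidates of which 3 are prognostic, and the baseline score in every model with an assumed correlation of 0.6 with follow-up. The true effect is 0 or 0.40 SD. The smaller effect is used because at 0.55 SD with baseline adjustment there is little room left to see a difference. Site and the health visitor pairing are not modelled.

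| Share of variance left after baseline that the 3 covariates explain | Baseline score only | Imbalance-selected | Pre-specified |
|---|---|---|---|
| 5% | 73.8% | 72.3% | 74.7% |
| 15% | 74.1% | 73.6% | 79.3% |
| 30% | 73.8% | 73.3% | 86.4% |

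- Gain of pre-specified over baseline score only: 0.9, 5.1 and 12.6 percentage points.
- Gain of imbalance-selected over baseline score only: none (−1.5, −0.5 and −0.5 points; the simulation error of one power figure is about 0.6 points).
- Type I error of the imbalance-selected model: 4.0–4.9% across all scenarios, including those with no baseline correlation.

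Check by formula: SE = √[(2/55)(1 − 0.6²)(1 − R²)], where R² is the share in the first column. This gives 0.153 at R² = 0 and 0.128 at R² = 0.30; the simulated values are 0.153 and 0.130.

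**What the undefined criterion leaves open.** A further simulation used 54 per arm, 13 candidates, baseline score always included, and 4,000 trials per scenario. It compared no selection with triggers of p<0.05, p<0.10 and p<0.20. Across these four choices the treatment estimate within one trial ranged over a median of 0.04–0.06 SD, and 0.09–0.14 SD at the 90th percentile.

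**The case against.** The strongest reply is that the plan already holds the adjustment that matters most. The baseline score of each outcome is always in the model and is usually the best predictor. With an assumed correlation of 0.4 to 0.7, it cuts residual variance to 84%–51% (1 − r²) and lifts power for 0.55 SD at 54 per arm from 81.5% to 88%–98%. If further covariates explained 10% of what remains, the SE would fall by about 5% (√0.90 = 0.949), and power would move only from about 88% to 91%, or from 98% to 99%. This stands. A reader might infer that all covariates are picked by imbalance, or that prognostic adjustment is lost altogether; the same sentences of the plan rule that out.

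A second reply is that the rule is announced in advance and uses baseline data, not outcomes. This also stands as far as error rates go. A reader might infer an inflated false-positive rate, but a mechanically applied rule is at or slightly below the nominal 5%. Only an analyst who reported the most favourable of the four triggers above would reach about 6–7%, and nothing in the protocol says anyone would do so.

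Third, the 49% rests on an assumed trigger and on independence, which is doubtful for pairs such as income and employment. Counting the baseline questionnaire scores as candidates would raise the figure, but some of these are already fixed in the models, so it should not be pushed higher on that ground.

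Fourth, the health visitor comparison is redundant but harmless, and drop-out can break pairs in the analysed data.

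The objection that an unseen analysis plan may settle the list does not stand. The protocol does not leave the choice open; it states a rule, and a fixed list would replace that rule.

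**Conclusion.** The point holds in limited form. For the primary and secondary models, covariates beyond the baseline score and site are selected by chance imbalance under an undefined criterion, so the primary model is not settled before the arms are compared. On the stated assumptions (p<0.05, 13 independent items) chance adds at least one covariate in about 49% of trials.

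The cost is discretion and forgone precision. Selection gains nothing over baseline-score adjustment, whereas covariates fixed in advance would add about 1 to 13 percentage points of power. That range assumes a 0.40 SD effect, a baseline correlation of 0.6, and extra covariates explaining 5–30% of the remaining variance. None of these values is in the protocol, and at the planned 0.55 SD the gain would be smaller.

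No bias or type I inflation follows from the rule itself, and the sample size is unaffected. This is a free improvement, not a validity error.

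**What to change.** In the Statistical analyses section, for primary and secondary outcomes alike, replace control for observed baseline differences with a short list fixed before the arms are compared: the baseline score of the outcome, study site, and a few expected predictors already collected, such as child age, child sex and baseline BDI.

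Describe baseline characteristics by arm without using the comparison to choose covariates. Label any adjustment prompted by observed imbalance as a sensitivity analysis. Drop the between-arm comparison of health visitor characteristics and describe the health visitors once, as a single group.

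The cost is wording only: no new data, no extra families and no change to the sample size.

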### Mediational analysis

Exploratory mediational analyses will examine the extent to which changes in child behaviour problems (as measured by the ECBI) are determined by the effects of the intervention on parent behaviour (as measured by the parenting behaviour categories of the DPICS observation tool and/or the Arnold-O’Leary Parenting Scale) and parental depression (as measured by the BDI). Analysis will be conducted using regression approaches with bootstrapping, as recommended by Dearing and Hamilton [45] using SPSS (SPSS Inc., Chicago, IL, USA) macros written by Preacher and Hayes [46].

### Moderator analysis

Indicators of poor outcome, as assessed by a demographic questionnaire, will be included in the regression models to determine whether any risk factors moderate the effect of the intervention on primary and secondary outcomes. Risk factors include lone parent, poverty, teenage parent, unemployment and low education level.

The presence of parental depression will be assessed using the BDI. This score will be collected at baseline and an interaction term (BDI * intervention group) will be included in the regression model to determine whether the intervention is less beneficial for children whose main caregiver demonstrates symptoms of depression.

### Missing data

Missing data will be managed using multiple imputation (MI). This has been found to be the most accurate method of dealing with missing data, regardless of whether it is missing at random or not [47]. Imputation strategies for MI will be reported and justified, and imputed data for MI analysed as part of a sensitivity analysis.

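### The stated reason for multiple imputation is wrong when drop-out depends on the outcome, and the article does not settle how drop-outs enter the intention-to-treat analysis

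*Protocol article*

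**What the plan says.** Protocol article, Statistical analyses: "The main analyses will be performed using the entire intention-to-treat population". The primary outcome is the ECBI change score, which "will be calculated for each individual and compared between conditions using multiple linear regressions", adjusted for baseline ECBI, study site and any baseline differences. A per-protocol analysis is added, restricted to "participants who have remained in the study and have completed measures at all time points".

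Protocol article, Missing data: the opening sentence makes MI the way missing data are handled. The next calls it "the most accurate method of dealing with missing data, regardless of whether it is missing at random or not" and credits a cited source. The last says that imputation strategies will be reported and justified, with "imputed data for MI analysed as part of a sensitivity analysis".

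Protocol article, Sample size: 55 families per arm for 0.55 SD at 80% power and 5% significance, raised to 60 per arm for 10% drop-out. The Abstract and the Intervention section give a single follow-up, about 6 months after baseline.

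**The concern.** There are two linked problems.

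First, the reason given for MI is wrong. Standard MI fills in a missing score from the relationship seen among families with data. If families leave because of how the child is doing, beyond what the imputation variables explain, the imputed scores carry the same bias as the observed ones. Agreement between an observed-data result and a MAR-based MI result would then look like robustness without being evidence of it.

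Second, the two sections do not fit together. A family without a follow-up ECBI has no change score. The main analysis can cover everyone randomised only if imputation, or some other method for missing outcomes, belongs to it, but the imputed data are placed in a sensitivity analysis. A reader cannot tell which estimate is primary. If that is settled after the data are seen, the primary result can be chosen.

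The setting makes non-random drop-out plausible. Parents know their allocation and report the primary outcome themselves. The programme asks for up to 12 weekly home sessions. Controls are waiting for an offer of treatment at 6 months, so reasons to stay may differ by arm.

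**Working it through.** **1. The plan's own figures.** Inputs from Sample size: effect 0.55 SD, power 80%, significance 5% (two-sided assumed), drop-out 10%.
- A two-sample t-test needs 52.9, so 53 per arm; the normal approximation gives 52. The stated 55 is within 2 of the t-test figure.
- Inflation: 55 / (1 − 0.10) = 61.1, so 62, against the stated 60. The sample size is not in dispute here.

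**2. Who is in an observed-data main analysis.**
- Completers per arm: 60 × 0.90 = 54, so 6 per arm (12 of 120) have no change score.
- t-test power at 0.55 SD is 81% with 54 per arm and would be 85% if all 60 were observed.
- The per-protocol set is defined by completing measures, not by adherence to the programme. If drop-out is the only reason for exclusion, it is also about 54 per arm, so the two analyses would use nearly the same families.

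**3. The two readings side by side.**

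| Reading | Fits | Conflicts with |
|---|---|---|
| MI is the main method | whole intention-to-treat population; MI handles missing data; separate completers set | imputed data placed in a sensitivity analysis |
| Observed-data regression is the main method | imputed data placed in a sensitivity analysis | whole intention-to-treat population; a change score for every individual; a distinct per-protocol set |

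Neither reading satisfies every sentence.

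**4. Does MI hold up whether or not data are missing at random?** This was checked by simulation. Assumptions: 120 families, true effect −0.55 SD, baseline to follow-up correlation 0.6, baseline-adjusted regression, MI from arm and baseline score with 20 imputations, 2,000 runs.

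| Drop-out mechanism (assumed) | Full data | Observed data only | MI |
|---|---|---|---|
| MAR, depends on baseline, about 10% | −0.547 | −0.547 | −0.546 |
| Depends on the unseen outcome in the intervention arm, about 11%; random 10% in control | −0.548 | −0.633 | −0.633 |

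The Monte Carlo standard error of the observed-data mean is about 0.003. Under outcome-dependent drop-out the bias is 0.633 − 0.548 = 0.085 SD, and 0.085 / 0.55 = 15%. MI removed none of it.

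**5. Size for a given departure.** If only intervention-arm drop-outs do worse than MAR predicts, bias = drop-out fraction × departure. The departures are assumptions.
- 0.10 × 0.5 = 0.05 SD, and 0.05 / 0.55 = 9%
- 0.10 × 1.0 = 0.10 SD, and 0.10 / 0.55 = 18%

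An apparent 0.55 would then stand for 0.50 to 0.45.

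**The case against.** Several stronger readings are tempting, and the article does not support them.

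- **That the main analysis is a complete-case analysis labelled intention-to-treat.** The article never says so. Missing data opens by making MI the general method, and a separate completers set suggests that the intention-to-treat analysis is meant to include non-completers. Nor does it say that MI is confined to the sensitivity analysis. What stands is a conflict between sections.
- **That the plan treats its claim as a reason to do nothing else.** It does not say that. It promises to report and justify the imputation strategies.
- **That non-random drop-out goes untested in the trial.** A statistical analysis plan that is not shown may contain such an analysis, so its absence from a journal article is no fault. The fault is the incorrect statement, together with a described sensitivity analysis that, as standard MI, rests on MAR.
- **That the article claims MI is valid under any mechanism.** It says most accurate, a comparison credited to a source not at hand. The comparison still fails in the simulation above, where MI was no more accurate than observed data under outcome-dependent drop-out.

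Two further objections bear on severity, and both carry weight. With one follow-up and baseline adjustment, the choice between MI and observed-data regression barely moved the estimate under either mechanism, so insisting on MI as primary would be preference. And leaving the programme is not the same as missing the outcome: researchers collect follow-up at home visits, with a small gift, separately from the health visitor's sessions. The article raises hard-to-reach families mainly as a challenge of recruitment and engagement and does not predict that dissatisfied intervention families will be lost.

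**Conclusion.** The point holds in two parts. The justification for MI is incorrect for standard MI, and a MAR-based imputation cannot serve as a check on outcome-dependent drop-out. Statistical analyses and Missing data also leave open whether drop-outs enter the main analysis through imputation or not at all; on the second reading it covers about 54 of 60 families per arm at the planned 10% loss.

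The bias figures are illustrative. The 0.05 to 0.10 SD depends on an assumed 0.5 to 1.0 SD departure confined to the intervention arm, and the simulated 0.085 SD on an assumed correlation and drop-out mechanism. None of these comes from the article. At 10% loss even the 1.0 SD departure leaves 0.45 SD, so this is below must-fix. It still deserves correction, because the article itself calls 0.55 optimistic and the primary estimate should be unambiguous.

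**What to change.** 1. In Missing data, delete the claim that MI is best whatever the missingness mechanism, and state that MI assumes MAR given the imputation model.
2. Reconcile Statistical analyses with Missing data. Before outcome data are analysed, name either MI or observed-data regression as the primary handling of missing follow-up ECBI, and describe the population to match. Either is defensible. If observed-data regression is chosen, do not describe the analysis as covering the whole intention-to-treat population, and say how it differs from the per-protocol analysis.
3. Make the sensitivity analysis a delta-adjusted MI that departs from MAR, for example by worsening imputed intervention-arm ECBI scores in steps from 0 to 1 SD, and report where, if anywhere, the conclusion changes.

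The cost is a few sentences and one extra analysis run. No new data are needed.
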